#### Kettle Test

The Kettle Test was developed as a brief performance-based measure to assess cognitive skills in a functional context. The test uses a standard set of items including an electric kettle (empty and disassembled parts); ingredients for beverages, presented on a tray together with other ingredients as distracters; and necessary dishes and utensils together with distracters. The task of preparing two hot beverages is broken down into 13 discrete steps that can be evaluated. All 13 steps of the task are scored on a 4-point scale. The total score ranges from 0 to 52 with higher scores indicating the need for greater assistance [39].

#### Face Washing Functional Task

The face washing task is not based on a standard scale. Participants will be asked to demonstrate for the observer the personal care activity of face washing. Qualitative observations will be noted, focusing on aspects of safety and independence.

#### Global Deterioration Scale

This scale assesses the stages of cognitive function in primary degenerative dementia. It is broken down into 7 different stages. Stages 1-3 are the mild stages of dementia. Stages 4-5 are the moderate stages of dementia. Beginning in stage 6, an individual can no longer maintain independence without assistance. Within the Global Deterioration Scale , each stage is numbered (1-7), given a short title (Mild, Moderate, etc), and followed by a brief listing of the characteristics for that stage. Caregivers can estimate the stage of an individual in the disease process by observing that individual's behavioral characteristics and comparing them to the Global Deterioration Scale [23].

#### Mini Mental Status Exam

The Mini Mental Status Exam (MMSE) is an 11-question measure that tests five areas of cognitive function: orientation, registration, attention and calculation, recall, and language. The maximum score is 30. A score of less than 24 is indicative of cognitive impairment. The MMSE takes about 5-10 minutes to administer and is therefore practical to use repeatedly and routinely. The instrument relies heavily on verbal response and reading and writing. Therefore, patients that are hearing and visually impaired, intubated, have low English literacy, or those with other communication disorders may perform poorly even when cognitively intact [40].

#### Montreal Cognitive Assessment

The Montreal Cognitive Assessment (MoCA) test is a one-page 30-point test administered in approximately 10 minutes [41]. The MoCA assesses several cognitive domains including short-term memory, visuospatial abilities, executive functions verbal fluency and abstraction, attention, concentration and working memory, and orientation to time and place. The MoCA is more sensitive to mild cognitive impairment compared to the MMSE, and has also been used to assess cognitive impairment in Alzheimer’s disease [42], frontotemporal [43], and vascular dementia [44].

#### Custom Caregiver Quality of Life Index

The custom caregiver quality of life index includes 10 questions about the impact of caring for a person with dementia, aspects of the caregiver’s life, and the caregiver’s mental well-being. Areas include alteration in daily routine, sleep, financial train, outlook, mental stain, guilt, frustration, impact of illness on family, and feeling well informed about dementia. Scores range from 1 (not at all) to 5 (very much) with higher scores indicating greater impact of caregiving on quality of life.

### Remote Assessment Tools

The remote assessment tools will be used by the Telegerontology team for clinical decision making through the intervention period (schedule of assessment described in Table 1). We anticipate some variation in the frequency of their administration, dependent on the individual.

#### Cohen Mansfield Agitation Inventory

The Cohen Mansfield Agitation Inventory is a caregiver’s rating questionnaire consisting of a list of 29 agitated behaviors, each rated on a 7-point scale of frequency. Ratings pertain to the two weeks preceding the administration of the Cohen Mansfield Agitation Inventory [26] and takes approximately 20 minutes to complete.

#### Cornell Scale for Depression in Dementia

The Cornell Scale for Depression and Dementia was developed to assess signs and symptoms of major depression in patients with dementia and measure caregivers’ rating of 19 items. Ratings are based on symptoms present in the past week. Each question is scored as: 0=absent; 1=mild or intermittent; 2=severe; and n/a=unable to evaluate. High scores indicate more symptoms of depression [27].

#### Caregiving Hassles Scale

The Caregiving Hassles Scale has been described above under primary outcomes.

#### Occupational Therapy Home Video Assessment

The research assistant will collect a detailed video of the home and living space based on a standard checklist developed by the specialized gerontology health care team’s Occupational Therapist (Table 2). The Occupational Therapist will then assess the video recordings and compile a detailed report of home safety recommendations for the PCP to review with the patient/caregiver (schedule of assessment described in Table 1).

### Time Tracking

#### Telegerontology Time Tracking

Telegerontology team members will log the time spent delivering support to families during the intervention period as well as all other related tasks such as chart review and report writing. This measure will be used to help address feasibility issues, to inform remote monitoring practices, and may also inform future cost-benefit analyses based on the study findings.

### Circle of Care Measures

Circle of care is defined as anyone who is involved in patient care and can include formal care providers and informal caregivers [45,46]. These measures will not be used as outcome measures, but rather to address the research objective to identify existing issues in rural areas when caring for people with dementia from the caregivers’ and primary care physicians’ perspectives (schedule of assessment described in Table 1).

#### Baseline Interviews

Baseline interviews will be completed in person by the research assistant who will visit participants, caregivers and PCPs in their respective communities. All interviews will be audio recorded and transcribed for analysis. The interviewer will be experienced with qualitative research methods and will attempt to elicit detail using reflexive probes based on the participants’ answers.

#### PCP Interview

Prior to the active study phase, all recruited PCPs will be asked to take part in a qualitative focus group. The interview will center around 3 main questions (Textbox 1).

#### Caregivers Interview

All caregivers will be asked to take part in a qualitative interview at baseline. The interview will center around two main questions (Textbox 1).

### Sample Size Calculation

Sample size was calculated based on regional population statistics rather than for statistical power, targeting 2.5% of the population of community-dwelling dementia patients in the target region. Based on prevalence estimates, 98.5/1000 Canadians over 40 years of age have dementia with 34% living at home. The total population for the entire recruitment region of the present study is approximately 38,490 suggesting that the total population of community-dwelling dementia patents is approximately 1,289. Therefore, we aim to recruit 42 participants for inclusion in this study accounting for a 30% dropout rate.

**Table 2 table2:** Occupational Therapy Home Safety Video checklist.

Video	Description
1	A short video walking from the driveway outside, going into the house through the usual entry door, straight through the kitchen/living area into the person's bedroom and then into the bathroom.
2	Kitchen (short video)
3	Bedroom (short video)
4	Bathroom (short video)
5	Living room (short video)
6	Stairs (short video)
7	Laundry (short video)

Qualitative interview questions.PCP Interview QuestionsDescribe the care required to manage people with dementia in their homes.From your point of view, how well are your patients being managed at home?How would you envision an ideal circle of care to maintain people with dementia in their homes?Caregivers Interview QuestionsFrom your point of view, how well are you managing the health of your loved one at home?In an ideal world, how could things be improved? What are the main challenges you experience? Have you had successes caring for your loved one?

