## Introduction

In 2011 the estimated prevalence of dementia in Canada was 340,000 with just under one-third (109,500) living at home [1]. Community-based dementia care relies heavily on family caregivers, with 92% of surveyed Canadians with dementia reporting friends or family members managing care and transportation. A further 58%-92% report family caregivers assisting with personal care, medical care, activities of daily living, meal preparation, and emotional support [1]. With such high demands on family caregivers of people with dementia, they are at increased risk of stress and burden [2], medical and psychiatric comorbidities [3,4], and social isolation [5]. Rates of dementia [6] and mortality [7] are also higher among caregivers, perpetuating and compounding the issue into a cycle of caregiving that leads to early disability, cognitive decline, and death. These detrimental effects of caregiving can also translate to negative consequences for people with dementia, including earlier institutionalization [8] and increased mortality [9]. Approaches that support the caregiver as well as the patient are therefore fundamental to community-based dementia care.

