### Study Design

#### Overview

The study was approved by the local research ethics authority. This is a cluster randomized feasibility trial assessing 4 rural regions (2 per study arm) comparing usual rural community-based dementia care to Telegerontology plus usual rural community-based dementia care. Using the opaque envelope method, the rural regions will be randomized to control or intervention after baseline assessment. The intervention will last 6 months with the measurement of outcomes taking place at baseline, after 6 months (post), with follow-up occurring 6 months (6-month follow-up) and 12 months (12-month follow-up) after cessation of the intervention.

The study population will include 22 “dementia triads” that consist of a community-dwelling older Canadian with moderate to late dementia, their family caregivers, and their PCP. The study will be carried out in communities located in rural areas of Newfoundland and Labrador, Canada but will be monitored remotely from the metropolitan city of St John’s, Newfoundland and Labrador. We define *rural* in this study to mean a community with less than 10,000 residents and a location that is greater than two hours’ drive from the metropolitan city, where specialist health services are located. Before randomization, recruitment will begin by enrolling PCPs from rural communities who will make initial contact with potential participants. Written informed consent will be obtained for every individual agreeing to participate in the study except in the case for an individual with advanced dementia who lacks capacity, in which case consent will be obtained from the substitute decision maker. Consent will be reviewed without the presence of the PCP in order to limit undue influence for participation in the study.

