### Study Strengths and Limitations

The proposed study has several notable methodological strengths. The initial home visit is designed to help build rapport between the Telegerontology physician and participants. This method is also in keeping with previous research, which suggests that telehealth has effectively supported assessment and follow-up when used in combination with an in-person interdisciplinary memory clinic assessment [12].

Next, the Telegerontology measurement framework, based on the ICF and Wilson-Cleary models provides in-depth, multi-factor profiles of participants contributing to a methodology that acknowledges the broad range of factors that can impact health planning and management of community dwelling people with dementia. Likewise, the inclusion of caregivers and PCPs as participants adds further depth to both characterizing and assessing participants with dementia by acknowledging and building on the role of the caregiver and PCP in the health care triad. The development of remote monitoring apps from existing validated scales to assess dementia and caregiver burden is also a methodological strength of this study.

There are also several limitations in the protocol. The relatively small sample size can be seen as a drawback, however, based on regional prevalence estimates, the sample size is realistic for the target population. There may also be considerable variability between participants within a group, further complicating statistical analysis. Next, the Telegerontology physician serves as both an interventionist and assessor. This has the potential to create bias, however the primary outcome measures were selected partially to address this issue since they are based on participant self-report/chart review rather than clinical assessment.

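### The over-40 dementia prevalence behind the sample size conflicts with the protocol's own national count and is applied to the region's total population, so the pool of 1,289 is overstated several-fold and the 2.5% target does not describe the planned N

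*Protocol article*

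**What the plan says.** The protocol article sets its sample size without a power calculation. In Sample Size Calculation it is described as "targeting 2.5% of the population of community-dwelling dementia patients in the target region". The inputs are a prevalence, "98.5/1000 Canadians over 40 years of age have dementia with 34% living at home", and a regional head count: "The total population for the entire recruitment region of the present study is approximately 38,490". From these the section concludes that the "total population of community-dwelling dementia patents is approximately 1,289", and then: "we aim to recruit 42 participants for inclusion in this study accounting for a 30% dropout rate". The Abstract and the Overview of the study design give the study population as 22 triads.

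The Introduction states the national burden as a count: "In 2011 the estimated prevalence of dementia in Canada was 340,000 with just under one-third (109,500) living at home".

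Study Strengths and Limitations answers the concern about small numbers by saying that, "based on regional prevalence estimates, the sample size is realistic for the target population".

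**The concern.** A rate and a count for the same disease in the same country should imply a believable population. Here they do not. The regional head count also carries no age restriction, although the rate does.

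The share of the regional pool is the only basis given for N, and the limitations section relies on the same prevalence to defend it. If the pool is several times smaller than stated, the planned enrolment is not a thin slice of a large population but a substantial part of a small one. That matters for a feasibility trial whose findings are meant to inform a full-scale RCT, because a reader who sets enrolment against 1,289 would conclude that many more patients remain to be recruited than is likely. The pool also precedes the eligibility limits (age 60 or over, Global Deterioration Scale 4 or greater, formal diagnosis, referral by the physician), which reduce it further.

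**Working it through.** **Inputs from the protocol article.** Sample Size Calculation: 98.5/1000 over 40; 34% at home; regional total 38,490; target 2.5%; dropout 30%; pool 1,289; recruitment 42. Introduction: 340,000 cases, 109,500 at home. Overview: 22 triads.

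**Inputs assumed (not in the documents).** Canada's total population 30-37 million; Canadians over 40, 13-18 million; share of the region over 40, 45-60%.

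**1. The plan's own figures reproduce.**
- Pool: 38,490 × 0.0985 × 0.34 = 1,289.
- Target: 0.025 × 1,289 = 32.2.
- With dropout: 32.2 × 1.30 = 41.9, printed as 42.

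So 98.5/1000 is the rate actually used, and it was applied to all 38,490 residents.

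**2. Rate against national count.**
- Implied Canadians over 40: 340,000 / 0.0985 = 3.45 million.
- Implied total population, if the regional at-home rate held nationally: 109,500 × 38,490 / 1,289 = 3.27 million.
- Conversely, 98.5/1000 among 13-18 million people over 40 would mean 1.28-1.77 million cases, which is 3.8 to 5.2 times the 340,000 stated.

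**3. Correcting the rate only** (all 38,490 residents still treated as over 40).
- Pool = 38,490 × 109,500 / 13 million = 324; with 18 million, 234.
- Excess = 1,289/324 = 4.0 to 1,289/234 = 5.5.

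**4. Correcting the rate and the age group.**
- Over-40 version, pool = 38,490 × f × 109,500 / P40. With f = 0.60 and P40 = 13 million, 195; with f = 0.45 and P40 = 18 million, 105. Excess 1,289/195 = 6.6 to 1,289/105 = 12.
- All-age version, pool = 38,490 × 109,500 / P. With P = 30, 34 and 37 million: 140, 124 and 114. Excess 9.2, 10.4 and 11.3.

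**5. A region older than the nation.** If its all-age rate is 1.5 to 2 times the national one (assumed; P = 34 million), the pool is 186-248 and the excess 5- to 7-fold. To reach 1,289 the region would need 1,289/124 = 10.4 times the national rate.

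**6. What the planned numbers represent.**

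| Number | Share of 1,289 | Share of 324 | Share of 105 |
|---|---|---|---|
| 22 triads | 1.7% | 7% | 21% |
| 32 (before dropout) | 2.5% | 10% | 30% |
| 42 (after dropout) | 3.3% | 13% | 40% |

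A true 2.5% of a pool of 105-325 would be about 3 to 8 patients.

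**The case against.** The strongest reply is that the size of the error depends on figures the documents do not give: Canada's population, the number over 40 and the region's age structure. The prevalence in Sample Size Calculation carries no citation, so its case definition cannot be checked, and a rural region may well be older than the country. All of this stands, and it is why the result is a range. It does not rescue 1,289: no plausible national population brings the rate and the count together.

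It is also fair to say that N is expressly not based on power, that significant results are not expected, and that data collection is complete. No estimate or test depends on the pool. Nor does the article say that recruitment yield, or the number of regions in a later RCT, will be worked out from 1,289; that use is a risk, not a stated plan. The word realistic is not disproved either, since enrolling 13-40% of a pool may be possible. What fails is the stated support for it.

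Some stronger readings should be resisted:

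- A reader might infer that the prevalence alone is ten times too high. Correcting it alone explains about 4- to 5.5-fold; the rest comes from applying an over-40 rate to residents of all ages.
- A reader might infer a misprint for 98.5 per 10,000, because 340,000 / 0.00985 = 34.5 million. That would fit a rate for all ages, while the text says over 40, so the documents do not establish it.
- A reader might make something of 34% at home against 109,500/340,000 = 32.2%. The difference moves the pool by about 5% and is immaterial here.

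**Conclusion.** The concern holds as an inconsistency with a several-fold effect. The prevalence cannot be reconciled with the national count in the Introduction, and it is applied to the wrong age group. On the assumed ranges (Canada 30-37 million, 13-18 million over 40, 45-60% of the region over 40), the pool is roughly 105-325 rather than 1,289. The excess is about 4- to 5.5-fold from the rate alone and about tenfold, range roughly 7 to 12, with both errors; a moderately older region falls in between.

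The documents do not support a single corrected pool or percentage. They do show that the 2.5% basis does not describe the planned enrolment, and that the regional prevalence argument in the limitations section has no sound figure behind it. The consequence is for the stated rationale and for recruitment feasibility, not for power or analysis.

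**What to change.** In Sample Size Calculation, use a prevalence and an at-home share that are sourced, refer to a stated age group and agree with the Introduction. Apply them to the regional population of that same age group. Restate the pool, and give the fraction of it that the planned N represents, in place of 1,289 and 2.5%. Leave N unchanged. The ranges above show the size of the problem and should not be copied in as the authors' estimates.

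In Study Strengths and Limitations, replace the statement that the size is realistic for the target population with the corrected fraction. If recruitment yield is reported to help plan the full-scale RCT, use the corrected pool as its denominator.

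The cost is one sourced figure, one recalculation and two changes of wording, with no effect on enrolment or data. The downside is that the stated feasibility of recruitment will look less favourable.

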**Methods:**

This is a cluster randomized feasibility trial with four rural regions in the province of Newfoundland and Labrador, Canada (2 regions randomly assigned to “intervention” and 2 to “control”). The study population includes 22 “dementia triads” that consist of a community-dwelling older Canadian with moderate to late dementia, their family caregivers, and their Primary Care Physician (PCP). Over the 6-month active study period, all participants will be provided an iPad. The intervention is intended as an adjunct to existing PCP care, consisting of weekly Skype-based videoconferencing calls with the Telegerontology physician, and other team members as needed (occupational therapist, physical therapist etc). Control participants receive usual community-based dementia care with their PCP. A baseline (pre-) assessment will be performed during a home visit with the study team. Post intervention, 6- and 12-month follow-up assessments will be collected remotely using specialized dementia monitoring applications and Skype calls. Primary outcomes include admission to long-term care, falls, emergency room visits, hospital stays, and caregiver burden.

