#### Inclusion Criteria

##### Dementia Patient/Caregiver Dyad

Community-dwelling adults aged ≥60 years will be screened by PCP for having a score of 4 or greater on the Global Deterioration Scale [23], and have a formal diagnosis of dementia based on the Diagnostic and Statistical Manual of Mental Disorders IV. Caregiver is defined as an individual who self-identifies as providing support with instrumental activities of daily living in an informal (friend or family) capacity and who was referred to the study by the PCP.

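### The stated sample size is internally inconsistent: 22 triads against a target of 42, and a derivation of 42 that does not match its own inputs

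*Protocol article*

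**What the plan says.** The Abstract (Methods) states "The study population includes 22" dementia triads. The Study Design overview repeats the number prospectively, "The study population will include 22", and defines a triad as one person with dementia, the family caregivers and the primary care physician.

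The Sample Size Calculation section gives a different number and the reasoning for it:

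- The basis: "Sample size was calculated based on regional population statistics rather than for statistical power".
- The target: "targeting 2.5% of the population of community-dwelling dementia patients in the target region".
- The rates: "98.5/1000 Canadians over 40 years of age have dementia with 34% living at home".
- The base: "The total population for the entire recruitment region of the present study is approximately 38,490", which the section turns into about 1,289 community-dwelling people with dementia.
- The result: "we aim to recruit 42 participants for inclusion in this study accounting for a 30% dropout rate".

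The limitations paragraph of the Discussion relies on this calculation: it defends the small sample as achievable in light of regional prevalence. The Results section reports that data collection finished in April 2017.

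**The concern.** The population-share calculation is the article's only justification of the trial's size, since power was expressly set aside. It has three faults as written.

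1. Two different sizes are given, in different units, and nothing connects them.
2. The prevalence is per 1,000 people over 40, but the number it multiplies is described as the whole population of the region.
3. The step from 2.5% of the pool to 42 does not deliver 2.5% of the pool after the stated 30% loss.

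At stake is whether a reader can tell how many triads were planned. The two figures differ by a factor of 42/22 = 1.9. In a study meant to inform the design of a full-scale trial, a gap between planned and enrolled numbers would be a feasibility result in its own right, so the reader needs to know whether such a gap exists.

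**Working it through.** **Inputs**, all from the Sample Size Calculation section unless noted: population 38,490; prevalence 98.5/1000 (over 40); share at home 34%; target fraction 2.5%; dropout 30%; stated pool 1,289; stated target 42. From the Abstract and overview: 22 triads.

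**Step 1: reproduce the pool.** 38,490 × 0.0985 × 0.34 = 1,289.03. This matches the stated 1,289, so the over-40 rate was multiplied by the full 38,490. The intermediate figure is 38,490 × 0.0985 = 3,791 people with dementia, about one in ten of a population labelled as total.

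**Step 2: reproduce the target.** 0.025 × 1,289 = 32.2.

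- 32.2 × (1 + 0.30) = 41.9, which rounds to the stated 42.
- 32.2 / (1 − 0.30) = 46.04, i.e. 46 or 47 depending on rounding.

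The article states no formula. The multiplication by 1.3 is inferred because it gives 42 and the division does not.

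**Step 3: what 42 delivers.** 42 × 0.70 = 29.4 completers; 29.4 / 1,289 = 2.28%, against the intended 2.5% (32.2 people).

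**Step 4: try to reconcile 22 with 42.**

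- *As triads.* The 42 is a number of people with dementia, and each triad has one, so 42 should mean 42 triads.
- *As persons.* 22 patient–caregiver pairs are already 44 people before any physician is counted; 42 people would be 21 pairs.
- *Through dropout.* 42 less 30% is 29.4. Reaching 22 needs a loss of 1 − 22/42 = 47.6%.
- *As a share of the pool.* 22 / 1,289 = 1.7%, not 2.5%.

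None of these works.

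**Step 5: size of the denominator problem.** The article does not give the share of residents over 40. Assuming 45% to 65%:

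| Assumed share over 40 | Pool | 2.5% of pool | Divided by 0.7 | 42 as share of pool |
|---|---|---|---|---|
| 45% | 580 | 14.5 | 20.7 | 7.2% |
| 50% | 645 | 16.1 | 23.0 | 6.5% |
| 60% | 773 | 19.3 | 27.6 | 5.4% |
| 65% | 838 | 20.9 | 29.9 | 5.0% |

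On these assumptions, 29.4 completers would be 3.5% to 5.1% of the pool (29.4/838 to 29.4/580), above the 2.5% target.

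**The case against.** The strongest reply is that little depends on this number. The trial was not sized for power, the analysis section expects no statistically significant findings, 2.5% is a convenience fraction, and enrolment was over when the article appeared. This stands, and it limits the severity.

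Second, 22 may be the number enrolled and 42 the number sought. The timing makes that plausible. A reader might therefore infer either that there were two competing targets or that recruitment fell short by nearly half. The article supports neither firmly: the overview words 22 as a plan, and no passage says it was achieved. The inconsistency is established; its cause is not.

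Third, 38,490 may be the count of residents over 40 with the wrong label. The arithmetic for the pool would then be right. The article cannot settle this, so an overstated pool cannot be asserted outright.

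Fourth, the dropout shortfall is small (29 against 32) and exists only if 1,289 is right. On a smaller pool, 42 recruits would exceed the 2.5% target. This also stands: the second and third faults should not be added together as if both reduced the sample. Nor should a reader take 22 to be a correctly derived target because it lies within the 21–30 range in the table; that range rests on an assumed age share.

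Two further inferences are tempting and fail. One is that the pool should have been restricted to the eligible group ("Community-dwelling adults aged ≥60 years" at the required disease stage). The section defines its denominator as community-dwelling people with dementia, so a narrower one is a preference. The other is that recruitment yield will be reported against 1,289. The article nowhere says so.

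**Conclusion.** The sample size statement is inconsistent and needs correcting. The firmest part is 22 triads against 42 participants, which no unit or dropout allowance in the article reconciles. The pool of 1,289 pairs an over-40 rate with a figure labelled total population, so one of the two is wrong. The possible overstatement (a true pool of about 580–840) rests entirely on the assumed 45–65% share over 40. The dropout step is a lesser point: 42 recruited implies about 29 completers, 2.3% of 1,289, where the stated fraction would need 46–47 recruited.

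Severity is minor to moderate. No power, error rate or treatment comparison is affected. What is affected is the reader's knowledge of the planned size and the one argument offered for it.

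**What to change.** - State one planned target, with its unit (triads, or people with dementia), in the Abstract, the overview and the sample size section. Say explicitly whether 22 is planned or achieved enrolment.
- State the age base of 38,490. If it covers residents over 40, correct the label and keep 1,289. If it covers all ages, recompute the pool and the percentage from the number of residents over 40, and adjust the Discussion sentence that relies on it.
- If 42 was the planned target, keep it and restate it as 42 recruited with about 29 expected to complete at 30% dropout. Give the matching percentage: 2.3% of 1,289, or the figure on the recomputed pool.

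The cost is text only, plus one census figure if the pool is recomputed. No additional enrolment and no change to the analysis are needed.
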